### Randomisation

Participants will be randomly allocated by blocked randomisation to the intervention and wait-list control group using the Statistical Package for the Social Sciences (SPSS V.24). Due to the small sample size, blocked randomisation is deemed an appropriate technique for reducing the risk of bias and ensuring equal allocation between groups [20]. The wait-list control group will not be provided with any materials relating to the intervention or recommendations on how they can improve on their current lifestyle habits to maintain a ‘true control’. Upon the completion of data collection at 3 months, participants in the wait-list control group will be offered access to the intervention. The randomisation procedure will be carried out by a researcher not affiliated with the study. Participant allocation will be placed in a sealed envelope and opened by the lead researcher upon completion of baseline data collection.

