### Participants

#### Eligibility criteria for participants

Adult males (≥ 18 years)Working part-time or full-time as a taxi driver in Northern IrelandHaving access to the internet and a smartphone that allows for the downloading of mobile applications.

As this is a feasibility randomised controlled trial, no formal power calculation will be completed to determine sample size. Recommendations on the appropriate sample size for pilot and feasibility studies vary greatly, with sample sizes ranging between 24 and 50 participants [57]. We have chosen a sample size of 30 for this study, as recommended by the National Institute for Health Research (NIHR) in the UK [30].

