### Recruitment

As a result of taxi drivers working both independently and for large companies, recruitment will be conducted via the online social media platform ‘Facebook’ to increase reach. This method of recruitment was employed previously for the recruitment of participants to aid in the co-design of the ManGuard intervention. A Microsoft Forms link, with a brief description of the study, will be posted into two separate Facebook groups dedicated to taxi drivers working across Northern Ireland, estimated as having 4200 members. The link will be posted weekly, with recruitment open for a duration of 17 months, ceasing once the target sample has been achieved. Those who are interested will provide their name and email address, with the lead researcher then sending a participant information sheet with the inclusion/exclusion criteria.

Those that meet the inclusion criteria will be invited to the Northern Ireland Clinical Research Facility (NICRF) to be formally recruited to the study and complete baseline testing. During the participants’ final visit to the NICRF, participants in the intervention group will be offered the opportunity to participate in the semi-structured telephone interviews as part of a process evaluation. Verbal consent will be obtained and recorded at the commencement of the telephone interview, with participants made aware of their right to withdraw from the interview at any time.

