ManGuard contains seven modules: (i) introduction and goal setting, (ii) being active (iii) eating well, (iv) managing stress, (v) smoking, (vi) alcohol, and (vii) keep accelerating, the latter to be used as a re-cap module. Each module was developed through an iterative process between the lead researcher and the PAG, prior to being refined through end-user input gathered during the focus groups. Initially, it was envisioned that participants would access modules in a sequential order, once per week, throughout the intervention period. However, end-user input recommended participants have access to the modules of their choice in any order, dependent on their preference. Therefore, the intervention period will last a total of 7 weeks in line with the number of modules available, with participants having the choice of which modules they wish to access. Each module will take no longer than 10 min to complete, with the content of each module focused on providing participants with brief and motivational information on the CVD-related behaviour or risk factor of interest. Content development was guided by published scientific recommendations, and steered by end-user input, to be delivered in a ‘tips and tricks’ format, providing short segments of text, and accompanied with images relevant to the taxi driver population. Each module uses positive and motivational language as a means of improving the likelihood of successful behaviour change.

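### One person opens the envelopes of a small blocked list and corresponds with later recruits, so the next arm is partly predictable; separate the roles and fix the order of invitation

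*Protocol article*

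**What the plan says.** Under Randomisation, the protocol article plans a two-arm blocked scheme: "Participants will be randomly allocated by blocked randomisation to the intervention and wait-list control group". It justifies the choice by sample size, saying that "blocked randomisation is deemed an appropriate technique for reducing the risk of bias and ensuring equal allocation between groups". A researcher outside the study carries out the procedure. The envelope step is: "Participant allocation will be placed in a sealed envelope and opened by the lead researcher upon completion of baseline data collection".

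Under Recruitment, men leave their details on a Microsoft Forms link, "with the lead researcher then sending a participant information sheet with the inclusion/exclusion criteria". Eligible men are then invited to one facility (NICRF). Recruitment may run for 17 months and stops at the target of 30. The sentences on invitation and formal recruitment name no person.

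Under Intervention, the lead researcher also has a part in the app: "Each module was developed through an iterative process between the lead researcher and the PAG". App users' questions go to the same person.

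**The concern.** The safeguards conceal one allocation at a time. They do not conceal the pattern of past allocations from the person who opens the envelopes. In a blocked 1:1 list that pattern carries information, because the arm that is behind is the likelier next one. The article credits blocking with reducing bias, but when someone in contact with later recruits holds the tally, blocking is also what makes the next arm partly foreseeable. Opening the envelope after baseline does not help here, since the guess is available before the man is invited.

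The eligibility criteria are objective, so the remaining levers are the timing of contact and the warmth of encouragement. Suppose keener men tended to arrive when ManGuard was due. App engagement is a primary outcome that comes only from the ManGuard arm (about 15 men) until the controls are offered access. It would look better than it is, and so would the acceptability interviews, which are limited to that arm. The secondary efficacy contrast would share the bias.

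**Working it through.** **Inputs.** Target 30 men (Eligibility criteria for participants); blocked, equal allocation, so 15 per arm if all are recruited (Randomisation); earlier allocations known to the person who opens the envelopes. Assumptions: envelopes are opened as men enrol, and there is one unstratified list. The block size is not stated, so a range is shown. The sizes that divide 30 into balanced blocks are 2, 6, 10 and 30.

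**The plan's own figure.** The 30 follows a recommendation and "no formal power calculation will be completed to determine sample size", so there is no formula to reproduce, and the number is not disputed.

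**Formulas.** For a balanced block of size 2m:

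- Expected assignments certain in advance, if the block size is known: 2m/(m+1) per block.
- Expected correct guesses when naming the arm that is behind, with a coin toss when level: m + ½(4^m / C(2m,m) − 1) per block.

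The second rule does not need the block size. Every completed block is balanced, so the overall difference between arms equals the difference within the current block.

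**Results for 30 men.**

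| Block size | Certain (size known) | Correct guesses |
|---|---|---|
| 2 | 15 × 1 = 15.0 (50%) | 15 × [1 + ½(4/2 − 1)] = 22.5 (75%) |
| 6 | 5 × 6/4 = 7.5 (25%) | 5 × [3 + ½(64/20 − 1)] = 20.5 (68%) |
| 10 | 3 × 10/6 = 5.0 (17%) | 3 × [5 + ½(1024/252 − 1)] = 19.6 (65%) |
| 30 | 30/16 = 1.9 (6%) | 15 + ½(6.92 − 1) = 18.0 (60%) |

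Simple randomisation gives 15.0 of 30 (50%). Simulated lists with mixed small blocks (2/4/6, 4/6 or 4/6/8; 40,000 lists each) gave 67% to 70% correct from the tally alone.

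**Ceiling on the bias.** Let keen and less keen men differ by d SD on an outcome. If a keen man filled every place guessed to be ManGuard and a less keen man every other place, the share of keen men would be g in ManGuard and 1 − g in control, where g is the share guessed correctly. The arms would differ by (2g − 1)d: 0.20d at block size 30, 0.37d at size 6 and 0.50d at size 2. This supposes perfect steering, and the documents give no value for d.

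**Effect of possible remedies.**

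- Blocks of 8, 10 and 12 in random order, tally still visible: correct guesses 5.33 + 6.53 + 7.72 = 19.6 (65%), the same as fixed blocks of 10. Certain assignments fall to about 8% (2.3 men), by simulation with the set of sizes known but not their order.
- Whoever contacts and schedules men does not know earlier allocations: 15.0 of 30 (50%), none certain.

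**The case against.** The strongest reply is that the lead researcher's only stated task before enrolment is correspondence: receiving expressions of interest and sending the information sheet. A reader might infer that one person both enrols and unseals, and so can place men at will. The article does not say that. Who screens, invites, schedules and takes consent is not stated, and a condensed article may leave this, like the block size, to the full protocol. Their absence is no finding. This part of the objection stands: the opportunity is inferred, and no steering is shown.

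A reader might also take the trial to be unmasked and unstratified. Neither is stated. An open design is likely, since the controls receive no materials, but Study design says the groups will be matched on demographics, which leaves balancing factors open. The figures are therefore conditional on one list.

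Steering would also be hard. Thirty men over 17 months is 30/17 = 1.8 a month if the full period is used, so there may be no queue to choose from, and discouraging a man would hurt recruitment. That makes the ceilings above unreachable in practice.

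Finally, if all envelopes were opened only after the last baseline, no sequential prediction would arise. The wording does not exclude this. However, assessments are timed from allocation, and recruitment may last 17 months, so early recruits could wait more than a year between baseline and allocation. Opening as men enrol is the natural reading.

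None of this removes the core point: the person who opens the envelopes is in contact with men not yet enrolled.

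**Conclusion.** The point holds in a limited form. The current man's allocation is concealed. Later allocations can be guessed better than chance, about 60% to 75% against 50%, by someone who corresponds with the men. It would be too strong to say that assignments are known: certainty applies to 6% to 50% of them, and only if the block size is known.

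Exposed are engagement and acceptability in the ManGuard arm and the secondary efficacy contrast, which the article already treats as unpowered and to be read with caution. The recruitment criterion does not depend on arm, the retention criterion is not stated as an arm comparison, and no stated progression threshold is shown to move. This is a cheap improvement to a stated procedure. It is still worth making, because the trial is meant to inform a definitive one and the process of randomisation is itself under evaluation (Progression criteria).

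The conclusion rests on envelopes being opened as men enrol and on a single list.

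**What to change.** Amend Recruitment and Randomisation in two respects.

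1. **Order of invitation.** Men are invited to NICRF strictly in the order of their time-stamped Microsoft Forms response. This removes discretion over timing, whoever does the inviting.
2. **Release of allocations.** The unaffiliated researcher holds the list and releases each allocation only after that man's consent and baseline data have been logged. Where possible it goes to an existing team member who does not handle contact and scheduling, so that whoever does so is unaware of earlier allocations. As the lead researcher also answers app users' questions, and may learn allocations that way, it may be simpler to give contact and scheduling to someone else.

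Undisclosed varying block sizes may be added to reduce the assignments known with certainty. Alone they leave about 65% guessable, so they are not the main remedy, and the arms may differ by a few men if recruitment stops short of 30.

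The cost is about a paragraph of text, a brief message per assignment and a small reallocation of tasks among existing staff. No extra participants or new systems are needed.

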### Intervention

The intervention is an eHealth program (ManGuard) that aims to reduce CVD risk in male taxi drivers. ManGuard was developed utilising a co-design approach, involving an ongoing collaboration between the research team, a computer scientist, and end-users (taxi drivers). Utilising co-design with an iterative approach is crucial for the success of an eHealth intervention [64]. First, an online survey was disseminated to gain an insight into life as a taxi driver in Northern Ireland and to guide the initial development of ManGuard. Utilising the iterative process between a Project Advisory Group (PAG) and focus groups with end-users, low-fidelity prototypes for the program and materials that would make up the ‘content’ where refined. The inclusion of behaviour change theory in the development of health interventions is reported as an essential component for improving their effectiveness [59]. The Behaviour Change Wheel (BCW) was incorporated throughout the development of ManGuard, providing a pragmatic framework and ensuring the incorporation of theory throughout [40]. Guided by the BCW worksheets [42], physical activity was identified as the behaviour anticipated to produce the greatest reduction in CVD risk in male taxi drivers. This was due to the long periods of sedentary time associated with the occupation, the likelihood of male taxi drivers changing the behaviour, the impact that physical inactivity has on other CVD-related behaviours, and the ease of measurement in a clinical trial. Next, it was specified that male taxi drivers should aim to complete greater levels of physical activity daily, in any setting, and with whomever they wish.

The next step in the process was to ensure the intervention was grounded in behaviour change theory, beginning with the conduction of a behavioural analysis. Doing so uncovers what needs modified at the individual level for successful change to occur. Next, the outcomes of the analysis were mapped to intervention functions deemed appropriate for facilitating the necessary change. Lastly, behaviour change techniques (BCTs) that could successfully deliver the intervention functions were identified using the BCT taxonomy [41], and through an assessment of BCTs utilised in previous eHealth interventions targeting male only participants [39]. ManGuard will be delivered as an application (app), accessible through handheld devices including mobile phones and tablets.

ManGuard contains seven modules: (i) introduction and goal setting, (ii) being active (iii) eating well, (iv) managing stress, (v) smoking, (vi) alcohol, and (vii) keep accelerating, the latter to be used as a re-cap module. Each module was developed through an iterative process between the lead researcher and the PAG, prior to being refined through end-user input gathered during the focus groups. Initially, it was envisioned that participants would access modules in a sequential order, once per week, throughout the intervention period. However, end-user input recommended participants have access to the modules of their choice in any order, dependent on their preference. Therefore, the intervention period will last a total of 7 weeks in line with the number of modules available, with participants having the choice of which modules they wish to access. Each module will take no longer than 10 min to complete, with the content of each module focused on providing participants with brief and motivational information on the CVD-related behaviour or risk factor of interest. Content development was guided by published scientific recommendations, and steered by end-user input, to be delivered in a ‘tips and tricks’ format, providing short segments of text, and accompanied with images relevant to the taxi driver population. Each module uses positive and motivational language as a means of improving the likelihood of successful behaviour change.

Program features include goal setting and self-monitoring of progress [72], including physical activity, diet, weight, smoking, and alcohol. A group messaging board was envisioned as being embedded into the program, providing an opportunity for enhancing social support, shown to be effective in promoting engagement in an eHealth intervention for men [26]. However, qualitative input from end-users highlighted a social forum as being potentially problematic due to the nature of this population, the language they use, and how they interact with each other. As a result, a Question and Answer (Q&A) page will be utilised during the initial testing of ManGuard. Questions will be sent directly to the lead researcher with the answers posted publicly for all users. The questions and answers will be used as the basis of a Frequently Asked Questions page for future iterations of the program if a definitive trial is deemed feasible. The program will be interactive, with in-app motivational messages displayed as a form of automated feedback. It is envisioned that the messages will provide positive reinforcement when they are progressing well towards their goals, or as messages of encouragement if progress is poor. Participants will be provided with in-app ‘awards’, badges they collect for achieving milestones such as completing a module or making progress towards a goal. Weekly push notifications will be employed as reminders to access the program and modules, with twice-weekly notifications delivered to users as a reminder to input and track progress.

### Data collection, management, and analysis

#### Demographic characteristics

A survey will be disseminated during the participants’ first visit to the NICRF to gather demographic data. Information will pertain to the participants’ age, postcode, education level, employment status, years worked as a taxi driver, working hours, lifestyle factors, knowledge of CVD, and presence of chronic diseases diagnosed by a health professional. The information gathered form the survey will be explored to gain an understanding of factors that may influence a participant’s decision to take part in the study.

#### Feasibility measures

As this is a feasibility randomised controlled trial, the primary outcomes of interest are the following:Recruitment ratesRetention ratesEngagement with the interventionAssessed by program usage via weekly analytics, including the quantity of participant logins, modules accessed, time spent on each module, and frequency of accessing the progress tracking systemProgram usability and participant satisfactionObtained as part of the process evaluation through semi-structured telephone interviews (Additional file 1) with a subset of participants. Telephone interviews will be conducted by a member of the research team who is trained and experienced in qualitative interviewing. Additionally, a satisfaction survey will be completed by all participants during the 3-month assessment time point.

#### Clinical indices

Though not powered to detect clinically significant change, the following CVD-related outcomes will be assessed to determine preliminary efficacy of ManGuard, and feasibility of each for inclusion in a definitive trial:

#### CVD biomarkers

CVD biomarkers will be assessed through point-of-care testing with the Alere Cholestech LDX Analyzer, valid for the analysis of cholesterol and glucose measurements [10, 52]. Participants will be required to fast for 8-h prior to testing.Full cholesterol breakdown (total cholesterol, HDL cholesterol, LDL cholesterol, triglycerides, and total/HDL cholesterol ratio)

#### Blood pressure

Systolic and diastolic blood pressure will be measured using a calibrated sphygmomanometer three times during each visit, with one-minute intervals between each. An average of the three measures will be calculated and used as the final reading [62]. Measurements will be taken from a seated posiiton by a trained member of the research team, with the cuff placed in line with the midpoint of the sternum. Participants will be asked to sit upright, feet flat on the floor, for 3–5 min prior to the first measurement being taken [47].

#### Anthropometry

BMIBody fat percentage will be analysed through Bioelectrical Impedance Analysis (BIA). BIA is a valid, precise, and cost-effective method of assessing body fat percentage and lean mass, both having strong correlations with mortality and morbidity [6]Waist circumference will be measured midway between the lowest rib and the iliac crest, proven to be the most reliable for defining central obesity [36].

#### Physical activity

Physical activity will be measured both objectively and subjectively using accelerometer data and the short-form version of the International Physical Activity Questionnaire (IPAQ-SF), respectively.Accelerometer data will be collected using the Actigraph GT3X + accelerometer, deemed a reliable tool for measuring physical activity in adults living in ‘free conditions’ [1]. Participants will be required to wear the accelerometer for 3–5 days to ensure the most reliable estimates of physical activity [61]The International Physical Activity Questionnaire (IPAQ-SF), a 7-item self-report survey of physical activity completed in the last 7 days, is a valid and reliable tool [15]. Items include frequency and intensity of physical activity, as well as time spent sedentary [15]. The IPAQ-SF has previously shown significant associations with accelerometer derived physical activity data (Murphy et al. 2017).

#### Psychosocial status

Psychosocial status will be assessed through health-related quality of life (HRQOL), self-efficacy, and social support measures.HRQoL will be assessed using the ‘generic’ 12-item Short Form Health Survey (SF-12) to measure physical and mental health components across the last 4 weeks [71]. The SF-12 has adequate scale reliability (Cronbach’s alpha = 0.89) and has been validated in the ‘general’ UK population [9].Self-efficacy will be assessed using the General Self-Efficacy Scale (GSE), a 10-item self-report measure of an individual’s self-belief in coping with a variety of difficult and demanding life tasks [34]. The GSE has demonstrated validity and reliability across 25 countries consisting of a variety of cultures and genders, with a Cronbach’s alpha of 0.88 in participants from Great Britain [56].Social support will be assessed using the Multidimensional Scale of Perceived Social Support (MSPSS). The MSPSS is a reliable, brief, and easy to complete [2] 12-item self-report measure of support from an individual’s family, friends and their significant other [77]. The MSPSS has strong internal reliability (Cronbach’s alpha of 0.93–0.98) in both clinical and non-clinical subjects, of different ages and gender [28].

The schedule for the enrolment or participants, administration of the intervention, and the outcomes with assessment time points is shown in Fig. 1.

